### Strength / power assessment

Handgrip strength will be measured to the nearest kilogram of each participant’s dominant hand using a Jamar hand dynamometer (Sammons Preston, Inc., Bolingbrook, IL) [80]. The dominant hand will be determined according to the lateral preference inventory [81]. The measurements will be performed with participants sitting in an upright position and with the arm of the measured hand unsupported and parallel to the body. The width of the dynamometer’s handle will be adjusted to each participant’s hand size so that the middle phalanges rested on the inner handle. We will instruct participants to exert maximal force. Starting with one submaximal trial to get accustomed to the testing procedure, participants will perform one maximal test trial. The intraclass correlation coefficient was calculated for handgrip strength (ICC = 0.99) [82]. Additionally, the Jamar hand dynamometer has been shown to have acceptable concurrent validity in young and adults [83].

Lower extremity strength / power will be assessed by the Chair Stand Test using a force platform (Leonardo 105 Mechanograph®) [84,85]. The Chair Stand Test will be performed as a clinical test, where participants will sit on a chair with their arms crossed on their chest, and stand up and sit down 5 times as quickly as they can. Time measured by a stop watch to the nearest 0.01 s indicates insufficient (≥16.7 s), sufficient (13.7 s to 16.6 s), good (11.2 s to 13.6 s), and very good strength performance (≤11.1 s) [85]. For the Chair Stand Test high test-retest reliability has been shown (ICC = .89) [86].

Participants will additionally perform maximal vertical countermovement jumps while standing on a force platform (Leonardo 105 Mechanograph®). The vertical ground reaction force will be sampled at 1,000 Hz. During the countermovement jumps, subjects stand in an upright position on the force plate and will be instructed to begin the jump with a downward movement, which will be immediately followed by a concentric upward movement, resulting in a maximal vertical jump. Subjects will perform three countermovement jumps with a resting period of 1 minute between jumps. For each of these trials, subjects will be asked to jump as high as possible. The best trial in terms of maximal jump height was taken for further data analysis. In a study by Granacher et al. [43] intraclass correlation coefficient was calculated for countermovement jumps power and amounted to ICC = 0.81.

The Stair Climb Power Test (SCP) will be used as a clinical equivalent for the countermovement jumps [87]. Participants will be instructed to safely ascend a 10-stair flight (each stair height 16.5 cm) as fast as possible. Use of the handrail will be allowed for safety reasons only. Timing begins after the countdown “ready-set-go” on the word “go” and stops when both of the participant’s feet reached the top step. Time will be measured by a stopwatch to the nearest 0.01 s and the average of 2 trials will be taken. SCP will be calculated by the formula: [power = force x velocity]. Test-retest reliability has been recorded and proved to be excellent (r = .99) [87].

### Assessment of body composition

A non-invasive bioelectrical impedance analysis (BIA) will be conducted before balance and strength / power assessments to minimize the effect of hydration status on measurements. Participants will be instructed to abstain from caffeine and alcohol 24 h, and exercise 12 h prior to testing according to published guidelines for BIA [88]. For BIA an octopolar tactile-electrode impedance meter (InBody 720, BioSpace, Seoul, Korea) will be used to estimate body composition according to the manufacturer’s guidelines. Multiple frequencies at 5, 50, 250 and 500 kHz will be used to measure intracellular and extracellular water separately. The participants will be measured under laboratory conditions standing barefoot on the device. With abducted arms 15° and legs 45° apart, they will hold a hand electrode with contact of all 10 fingers while the heels and forefeet will be placed appropriately on the foot electrode. Then an alternating current of 250 mA of intensity will be applied to measure impedance of arm, trunk and leg muscles. Whole-body resistance will be calculated as the sum of segmental resistance (right arm + left arm + trunk + right leg + left leg). The BIA with InBody 720 has been validated by dual-energy X-ray absorptiometry (R^2^ = 0.93) [89]. In normal and overweight adults multiple frequency BIA underestimated percentage of body fat within the precision of the BIA instrument (2%) [88,89].

### Design of exercise interventions

Study participants will be randomized (http://www.randomizer.org) with a gender ratio of 1:1 into 2 intervention groups (INT1 and INT2) and a control / waiting group (CON). The first intervention group (INT1) will conduct a 12-week exercise program according to the practice guide developed by the expert panel. The program consists of task-specific exercises for (1) static steady-state balance, (2) dynamic steady-state balance, (3) proactive balance, (4) reactive balance, and (5) strength as well as (6) power, especially for the lower extremities and the trunk muscles. Exercises will be performed 3 times per week on non-consecutive days, twice supervised for 45 min. (incl. 15 min. for warm-up and cool-down), and once at home for 30 min. individually. The second intervention group (INT2) follows the same exercise routine as the first intervention group (INT1), except that they perform a short version of the program called '3 times 3’. After a supervised introduction into the '3 times 3’ program, INT2 will individually train at home 3 times per week for 30 min. Each '3 times 3’ training session will consist of only one exercise within the 3 domains (static balance, dynamic balance, and strength). Quality and quantity of exercises will be controlled by weekly phone calls and a training log book. The control / waiting group will not participate in any form of training during the experimental period, but will receive the extensive supervised program after the experimental period. Pre and post assessment of all variables for all groups (INT1, INT2, CON) will be performed before and after the 12-week intervention period. Follow-up measurements 12 weeks after the intervention cessation will allow the assessment of detraining effects. Duration of a single assessment amounts to 90 min per participant.

### Intervention program

The expert panel selected balance and strength / power exercises which can be performed with one’s own bodyweight or with the help of small, low-cost exercise equipment (i.e., small weights, resistance bands, unstable surfaces). However, intensity control for strength / power exercises performed with one’s own bodyweight is more complicated compared to when using strength training machines. In this study, intensity during training will be regulated using the Borg Rating of Perceived Exertion scale (i.e., 6–20 points, maximal exertion at 20 points) [90]. According to the individual fitness level, exercises should be performed with a perceived exertion between 10 and 16 points (light to hard) during balance and strength / power training. Exercise intensity will be progressed individually using the Borg Rating of Perceived Exertion scale and varying the balance and strength / power exercises in order to sufficiently stimulate the neuromuscular system [91]. Rate of perceived exertion will be adjusted every 2 weeks by the therapist (INT1) or via phone calls (INT2). Strength / power exercises will be progressed from single to multiple joint, isometric to dynamic muscle contraction, short to long lever arm and slow to fast exercises [92]. Further details regarding the contents of the intervention program are described in Tables 1 and 2 for strength / power training, and Tables 3 and 4 for static and dynamic steady-state, proactive, and reactive balance training (see also Figures 2, 3 and 4).

**Figure 2 F2:**
[figure not shown]
**Base of support during static steady-state balance. (A)** bipedal stance, **(B)** semi-tandem stance, **(C)** tandem stance, **(D)** monopedal stance.

**Figure 3 F3:**
[figure not shown]
**Base of support during dynamic steady-state balance. (A)** normal gait, **(B)** narrow gait, **(C)** overlapping gait, **(D)** tandem gait.

**Figure 4 F4:**
[figure not shown]
Exercise progression and variation during training.

**Table 1 T1:** Guidelines for heavy resistance strength training

**Exercise variables**	**Recommendations**
Intensity	Defined by level of difficulty, fatigue and number of repetitions
	Beginner: 12 – 13 RPE (somewhat hard)
	Advanced: 14 – 16 RPE (hard)
Quality	Technically correct movement
	Maximal range of motion
Speed of movement, contraction velocity	2 s concentric muscle contraction, 2 s eccentric muscle contraction (ratio 1:1)
Sets	2 – 3 (at home 3 sets)
Frequency	2 group sessions per week and 1 session alone at home (alternating strength / power and balance training)
Repetitions	Beginner: 10 – 15 (moderate resistance until muscle fatigue)
	Advanced: 8 – 12 (high resistance until muscle fatigue)
Rest	2 min. between sets

*RPE* rate of perceived exertion.

**Table 2 T2:** Guidelines for muscle power training

**Exercise variables**	**Recommendations**
Intensity	Defined by level of difficulty, fatigue and number of repetitions
	10 – 13 RPE (light to somewhat hard)
Quality	Technically correct movement
	Maximal range of motion
Speed of movement, contraction velocity	Concentric contraction as fast as possible
	Approx. 1 s concentric muscle contraction, approx. 2 s eccentric muscle contraction (ratio 1:2)
Sets	2 – 3 (at home 3 sets)
Frequency	2 group sessions per week and 1 session alone at home (alternating strength / power and balance training)
Repetitions	8 – 10
Rest	2 min. between sets

*RPE* rate of perceived exertion.

**Table 3 T3:** Guidelines for static steady-state, reactive, and proactive balance exercises

**Balance (static)**	**Exercise variables**	**Recommendations**
Steady-state	Base of support	Stable to instable: bipedal – semi-tandem – tandem – one leg stance (Figure 2)
	Position of feet	i.e., lateral or medial weight shift, on heels or toes, toe angle in or out
	Surface	i.e., from soft to hard (e.g., grass to concrete), from stable to instable (e.g., concrete to sand)
	Sensory input	Impede vision or hearing
	Dual-/Multi-tasking	Additional motor task – additional cognitive task – additional motor and cognitive tasks
	Speed of movement	Decrease or increase of execution speed (i.e., upper arm movements)
	Equipment	Use of i.e., free weights, elastic bands, balls
Reactive	Controlled perturbations applied by therapist	Reaction to external thread (push or pull) varying in speed, amplitude and direction on ankle, hip, trunk or shoulder level
Proactive	ADL	Combination of steady-state (static) balance tasks with mobility in daily life (e.g., standing up from a chair while reciting a poem and holding a cup of water)

*ADL* activities of daily living.

**Table 4 T4:** Guidelines for dynamic steady-state, reactive, and proactive balance exercises

**Balance (dynamic)**	**Exercise variables**	**Recommendations**
Steady-state	Base of support	Stable to instable: normal gait – narrow gait – overlapping gait – tandem gait (Figure 3)
	Position of feet	i.e., lateral or medial weight shift, on heels or toes, toe angle in or out
	Surface	i.e., from soft to hard (e.g., grass to concrete), from stable to instable (e.g., concrete to sand)
	Sensory input	Impede vision or hearing
	Dual-/Multi-tasking	Additional motor task – additional cognitive task – additional motor and cognitive tasks
	Speed of movement	Decrease or increase of execution speed (i.e., walking speed)
	Equipment	Use of i.e., free weights, elastic bands, balls
	Direction	Forwards – backwards – to the left or right – diagonal
	Rhythm	Slow – fast – intermittent slow and fast
Reactive	Controlled perturbations applied by therapist	Reaction to external thread (push or pull) varying in speed, amplitude and direction on ankle, hip, trunk or shoulder level
Proactive	ADL	Combination of steady-state (dynamic) balance tasks with mobility in daily life (e.g., walking upstairs backwards while counting backwards aloud from 50 minus 2)

*ADL* activities of daily living.

### Statistics and sample size

An a priori power analysis was conducted to detect the sample size that is necessary to find statistically significant exercise effects [93] based on a study assessing the effects of balance training on postural control in older adults [94]. Considering a dropout rate of 10%, 18 participants per arm will be required to achieve 90% power (type II error of 0.10) with a type I error of 5%. Data will be analysed using a 2- and 3-way repeated measures analysis of variance (ANOVA) consisting of groups (INT1, INT2, CON) and time (pre-test, post-test, follow-up). Bonferroni post-hoc test will be used for statically significant (p < .05) group and time differences. Associations between clinical and biomechanical tests will be reported by their correlation coefficient (r value), level of significance (p value) and the amount of variance explained (r^2^ value). Values of r = 0.10 indicate a small, r = 0.30 a medium and r = 0.50 a large-size correlation [i.e., effect size] [95].

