The current trial will add valuable information to the knowledge of dose–response-relations for exercise in older adults. Particularly the use of two different intervention arms (extensive supervised group exercise program vs. short home-based exercise program) will give some indication of the minimal amount of exercise needed to stimulate physical performance adaptations. If the short version of the program (3 times per week for 30 min.) will prove to be effective, this may lower the barrier for sedentary older adults to take up exercising. If intrinsic fall risk factors can be positively influenced by our proposed intervention regime, future trials will need to investigate any possible effect on fall rate in older adults. Additionally, in this trial, each clinical test will be compared to a gold-standard instrumented test. This cross-validation may facilitate the implementation of easy-to-administer balance and strength / power assessments into practice. Regular simple balance and strength / power assessments are important for training prescription and performance regarding exercise variation and progression. Furthermore, measuring gait velocity, grip strength and muscle mass will allow diagnosis of sarcopenia according to EWGSOP criteria, and may add knowledge to sensitivity and specificity of strength / power test to this important geriatric syndrome.

In summary, this trial will provide insight into the effect of fall prevention exercise applicable for a broad population and setting, both in community and sporting groups and at home. Practitioners, exercise therapists, and instructors will be provided with a feasible, validated exercise routine whose effect on intrinsic fall risk factors is scientifically evaluated. Furthermore, older adults who participate in the present program represent possible multipliers for a broader acceptance of important exercise and health-enhancing measures. Finally, the results of the current trial may help to further develop theories and models explaining balance and resistance training effects in general and particularly in older adults.

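### The stated 90% power, 5% error and arm-by-time ANOVA assume independent participants, although INT1 alone trains in therapist-led groups; any training-group correlation would weaken the INT1 contrasts

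*Protocol article*

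**What the plan says.** All references are to the protocol article.

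- **Sample size and power** (Statistics and sample size): after allowing for 10% dropout, "18 participants per arm will be required to achieve 90% power (type II error of 0.10) with a type I error of 5" per cent. The calculation rests on a cited balance-training study; no effect size or standard deviation is printed.
- **Analysis** (same section): a "repeated measures analysis of variance (ANOVA) consisting of groups (INT1, INT2, CON) and time (pre-test, post-test, follow-up"), followed by Bonferroni post-hoc tests. No training-group or therapist term is named.
- **INT1 delivery**: Tables 1 and 2 specify "2 group sessions per week and 1 session alone at home". The section on the design of the interventions says that the two non-home sessions are supervised. Tables 3 and 4 have the therapist apply the perturbations in reactive balance training.
- **INT2 and CON delivery** (same section): INT2 trains individually at home after a supervised introduction, with weekly phone calls. CON does not train during the experimental period.
- **Intensity control** (Intervention program): "Rate of perceived exertion will be adjusted every 2 weeks by the therapist (INT1) or via phone calls (INT2").
- **The comparison of the two active arms** (Discussion): "extensive supervised group exercise program vs. short home-based exercise program".

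**The concern.** Participants are randomised individually, but those in INT1 then spend 12 weeks in shared sessions under a therapist. Their post-test and follow-up values may share a component due to the class or the therapist. The other two arms have no comparable shared sessions. This is a partially nested design: clustering arises in one arm, after randomisation.

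An ANOVA on arm and time has no place for that component. If it exists, the INT1 mean varies more than the model allows, and both contrasts involving INT1 are tested against too small a standard error. Those contrasts matter most: the abstract expects benefit above all from the supervised programme, and the Discussion uses INT1 against INT2 to judge how little exercise is enough. An unusually good or poor class or therapist could be read as an effect of the programme.

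**Working it through.** **Inputs from the document.** 18 per arm, 54 in total, 10% dropout, 90% power, 5% type I error, three arms, Bonferroni post-hoc tests.

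**Inputs assumed, because the document does not give them.** Two-sided testing; training-group size m of 4, 8 or 16 (four, two or one INT1 groups); ICC of 0.01, 0.05 or 0.10.

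**Step 1: the plan's own figures.** 16 / 0.9 = 17.8, rounded up to 18, and 3 x 18 = 54. The dropout step and total are consistent with 16 completers per arm. The figure of 16 itself cannot be re-derived without an effect size.

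**Step 2: effect implied by the stated power under independence.** For a pairwise contrast with 16 per arm, normal approximation:
d = (1.960 + 1.282) x sqrt(2/16) = 1.146. (The t-test version is 1.18.) This serves only as a reference effect that has 90% power when ICC = 0.

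**Step 3: clustering in INT1 only.** Design effect DE = 1 + (m - 1) x ICC; effective INT1 n = 16 / DE; correct standard error of INT1-CON = sqrt((DE + 1) / 16); power = Phi(d / SE - 1.960).

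Two worked cells:
- m = 8, ICC 0.05: DE = 1 + 7 x 0.05 = 1.35; effective n = 11.9; SE = sqrt(2.35/16) = 0.383, against 0.354 under independence; power = Phi(1.146/0.383 - 1.960) = 84.9%.
- m = 16, ICC 0.10: DE = 1 + 15 x 0.10 = 2.5; effective n = 6.4; SE = sqrt(3.5/16) = 0.468; power = Phi(1.146/0.468 - 1.960) = 68.8%.

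**Step 4: type I error of the planned kind of test.** Simulated under no true effect: three arms of 16, one score per person, variance pooled over arms, INT1 clustered as assumed, and no allowance for clustering in the test. The columns give the omnibus test at 5% and the INT1-CON comparison at the Bonferroni level 0.05/3 = 1.67%.

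| m | ICC | Effective INT1 n | Power, correct SE | Omnibus error | INT1-CON error (nominal 1.67%) |
|---|---|---|---|---|---|
| any | 0 | 16.0 | 90.0% | 5.0% | 1.7% |
| 4 | 0.01 | 15.5 | 89.6% | 5.2% | 1.8% |
| 4 | 0.05 | 13.9 | 87.8% | 5.7% | 2.1% |
| 4 | 0.10 | 12.3 | 85.6% | 6.6% | 2.6% |
| 8 | 0.01 | 15.0 | 89.0% | 5.5% | 1.9% |
| 8 | 0.05 | 11.9 | 84.9% | 6.8% | 2.7% |
| 8 | 0.10 | 9.4 | 79.7% | 9.1% | 3.9% |
| 16 | 0.01 | 13.9 | 87.8% | 5.8% | 2.0% |
| 16 | 0.05 | 9.1 | 78.9% | 9.1% | 4.0% |
| 16 | 0.10 | 6.4 | 68.8% | 13.6% | 7.1% |

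Repeat runs differ by about 0.2 percentage points. INT1-INT2 behaves like INT1-CON. INT2-CON stays close to its nominal level throughout.

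**Limits.** The power column is for an unadjusted two-sided 5% contrast. It uses a large-sample formula that ignores the few degrees of freedom left by one to four groups, so it is optimistic. The simulation reduces the repeated measures design to one score per person.

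**The case against.** The strongest objection is that the size is unknown. The document gives no ICC, no number or size of INT1 groups and no number of therapists. Intensity is tailored to the individual, one session in three is done alone at home, and nothing says that groups are fixed or that one therapist leads each. The cited study's variance may already reflect group training; that cannot be checked. All of this stands. A reader might infer that INT1's effective sample is in fact smaller and its intervals in fact too narrow. The document does not support that: both follow only if the ICC is above 0, and the loss could be under 1 point of power or over 20.

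A second tempting reading is that INT1-CON is falsely positive far more often than 5%. An unadjusted two-arm t-test on one class of 16 at ICC 0.10 does give about 14%, but that is not the planned post-hoc test. At the Bonferroni level the INT1-CON error passes 5% in one cell of the table only. Inflation relative to the nominal 1.67% remains, and so does inflation of the omnibus test, so neither pooling nor Bonferroni removes the problem.

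A third objection is scope: group numbers and a clustering analysis often sit in a full protocol or SAP. That is fair for those details, and their absence is not the point. The article itself states the error rates and the model factors, and both rest on independence in an arm that it describes as group-delivered.

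Finally, INT2 participants also share an introduction and may share a caller, so treating INT2-CON as unaffected is itself an assumption.

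**Conclusion.** The concern holds conditionally. The stated power, error rate and ANOVA assume independence that INT1's delivery may break. If the training-group ICC is above 0, standard errors for INT1-CON and INT1-INT2 are too small and the 90% is optimistic.

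The size depends on assumed values. With 16 completers per arm, groups of 4 to 16 and ICC 0.01 to 0.10, the omnibus error lies between about 5.2 and 13.6%, the Bonferroni INT1-CON error between about 1.8 and 7.1%, and the power of an INT1 contrast that would have 90% under independence between about 89.6 and 68.8%. At ICC 0.01, or with groups of 4, the effect is minor. It becomes material with groups of about 8 or more and an ICC of about 0.05 or more. The power figures are not this trial's actual power, since its design effect size is not printed.

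**What to change.** 1. Restate the 90% power as holding only without clustering in INT1. Beside it, give the power for an INT1 contrast over ICC 0.01 to 0.10 at the actual training-group size.
2. Record each INT1 participant's training group and therapist. Pre-specify a sensitivity analysis for INT1-CON and INT1-INT2 that multiplies the variance of the INT1 mean by 1 + (m - 1) x ICC over that range. If there are several fixed groups, a mixed model with a random training-group effect in INT1 only and small-sample degrees of freedom can be used instead; with two to four groups that variance will be poorly estimated.
3. Report whether the INT1 conclusion holds across the range. If INT1 trains as one class, state that class or therapist effects cannot be separated from the programme effect; no model can do so.

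This should remain a sensitivity analysis. Allowing an INT1 claim only if it survives one chosen ICC would hang the main conclusion on a number without support in the document.

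The cost is a group and therapist identifier in the attendance list and a few lines of analysis text, with no extra participants or staff. Identifiers not recorded during training may be hard to recover later. The downside is wider INT1 intervals and a less favourable stated power.

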**Methods/Design:**

Healthy old people (n = 54) between the age of 65 to 80 years will participate in this trial. The testing protocol comprises tests for the assessment of static / dynamic steady-state balance (i.e., Sharpened Romberg Test, instrumented gait analysis), proactive balance (i.e., Functional Reach Test; Timed Up and Go Test), reactive balance (i.e., perturbation test during bipedal stance; Push and Release Test), strength (i.e., hand grip strength test; Chair Stand Test), and power (i.e., Stair Climb Power Test; countermovement jump). Further, body composition will be analysed using a bioelectrical impedance analysis system. In addition, questionnaires for the assessment of psychosocial (i.e., World Health Organisation Quality of Life Assessment-Bref), cognitive (i.e., Mini Mental State Examination), and fall risk determinants (i.e., Fall Efficacy Scale – International) will be included in the study protocol. Participants will be randomized into two intervention groups or the control / waiting group. After baseline measures, participants in the intervention groups will conduct a 12-week balance and strength / power exercise intervention 3 times per week, with each training session lasting 30 min. (actual training time). One intervention group will complete an extensive supervised training program, while the other intervention group will complete a short version ('3 times 3’) that is home-based and controlled by weekly phone calls. Post-tests will be conducted right after the intervention period. Additionally, detraining effects will be measured 12 weeks after program cessation. The control group / waiting group will not participate in any specific intervention during the experimental period, but will receive the extensive supervised program after the experimental period.

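### The post-hoc rule is triggered by group and time differences, and the article never names the between-arm difference in change as the efficacy test

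*Protocol article*

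**What the plan says.** The Statistics and sample size section gives the model in one sentence: "Data will be analysed using a 2- and 3-way repeated measures analysis of variance (ANOVA) consisting of groups (INT1, INT2, CON) and time (pre-test, post-test," with follow-up as the last time level. Two- and three-way versions are announced, but only two factors, group and time, are listed. The pre-test is one of the three levels of time, and no covariate is named.

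The next sentence sets the follow-up testing: "Bonferroni post-hoc test will be used for statically significant (p < .05) group and time differences". Neither that section nor any other names the group-by-time interaction, or a contrast between arms in change from pre-test.

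Under Design of exercise interventions, participants are randomised "with a gender ratio of 1:1 into 2 intervention groups (INT1 and INT2) and a control / waiting group (CON"). Gender therefore enters the allocation, but it is not listed as a factor in the analysis.

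On size, the article says: "Considering a dropout rate of 10%, 18 participants per arm will be required to achieve 90% power (type II error of 0.10) with a type". Alpha is set at 5%. The calculation is "based on a study assessing the effects of balance training on postural control in older adults". The article itself states no effect size, standard deviation or pre-post correlation.

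**The concern.** In a parallel-group trial measured before training, after training and 12 weeks later, the training effect is the difference between arms in how much they change. Group and time are the two factors that the ANOVA sentence has just listed, so the post-hoc trigger reads most naturally as a significant result on one of those factors. Neither isolates the training effect:

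- The group effect averages over all three visits, including the pre-test, where randomisation makes the true difference zero.
- The time effect averages over all three arms, including the untrained control arm. Any gain from repeating the same performance tests therefore counts towards it.

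At stake are two opposite errors. A trial with no training effect could report significant improvement over time, and a real difference between arms could go undetected because it has been averaged down.

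A separate and smaller matter is that the pre-test is handled as an outcome level, which gives up some precision compared with using it as a covariate.

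**Working it through.** **Inputs from the article.** Three arms, three visits, type I error 5%, 18 per arm, 10% dropout. Completers: 18 × 0.9 = 16.2, taken as n = 16 per arm and N = 48.

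**The article's own figure.** The 18 per arm cannot be reproduced, because the effect size, SD, correlation, test and sidedness are not given. Only the dropout step can be checked: 16 / 0.9 = 17.8, rounded up to 18, which is consistent.

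**Assumptions.** SD 1 at each visit; equal correlation ρ between visits, from 0.5 to 0.8; retest gain 0.2 to 0.5 SD; illustrative training effect d = 0.8 SD at post-test in both training arms, of which a fraction r is retained at follow-up.

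**1. Share of the effect in the group main effect.** The average over visits is (0 + d + r·d)/3. For r = 0, 0.5 and 1 this is d/3, d/2 and 2d/3. With d = 0.8 it is 0.27, 0.40 and 0.53 SD.

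**2. Power under a real effect.** For the group effect the noncentrality is n·m·Σ(arm mean − grand mean)² / (1 + (m − 1)ρ), with m = 3 visits. Example with ρ = 0.5 and r = 1: arm means 0, 0.533 and 0.533; grand mean 0.356; sum of squares 0.190; noncentrality 48 × 0.190 / 2 = 4.55 on 2 and 45 df; power 44%. Simulation (2,000 runs per row) gave:

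| ρ | r | Group effect | Group-by-time | ANCOVA at post-test |
|---|---|---|---|---|
| 0.5 | 0 | 13% | 64% | 74% |
| 0.5 | 0.5 | 26% | 51% | 74% |
| 0.5 | 1 | 44% | 64% | 72% |
| 0.8 | 0 | 12% | 98% | 97% |
| 0.8 | 0.5 | 21% | 92% | 97% |
| 0.8 | 1 | 35% | 98% | 97% |

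If the effect is instead set to give the interaction 90% power, the group effect has 20% to 69% power with half to full retention, and 10% to 22% with none (ρ 0.5 to 0.8).

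**3. Time effect under retest learning alone.** The noncentrality is N·Σ(visit mean − grand mean)² / (1 − ρ). With means 0, 0.3 and 0.3 in every arm, the sum of squares is 0.04 + 0.01 + 0.01 = 0.06, and 48 × 0.06 = 2.88. Dividing by 1 − ρ gives 5.76, 9.6 and 14.4 for ρ = 0.5, 0.7 and 0.8. On 2 and 90 df the chance of significance is 55%, 78% and 93%. Simulation (4,000 runs each) agrees at 56%, 79% and 93%, while the interaction and the post-test ANCOVA stay near 5%. Over gains of 0.2 to 0.5 SD, the time effect is significant in 27% to 95% of trials at ρ = 0.5 and 59% to 100% at ρ = 0.8.

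**4. Precision from baseline adjustment.** The contrast variance relative to a change score is (1 − ρ²) / (2(1 − ρ)) = (1 + ρ)/2. That is 0.75 at ρ = 0.5, 0.85 at 0.7, 0.90 at 0.8 and 0.95 at 0.9.

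**The case against.** The strongest reply is that the article does not say main effects. It says differences, and a group and time repeated measures ANOVA produces the interaction by construction. The sentence could mean pairwise comparisons between groups and times after that ANOVA. The concurrent control arm exists to separate learning from training, and the interaction uses it correctly: it stays near 5% under pure retest learning. All of this stands. It limits the point to an efficacy test that is never named and a trigger that, on its natural reading, points elsewhere.

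Several further replies also hold:

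- A reader might infer that the lack of baseline or gender adjustment produces the learning artefact or the dilution. It produces neither. The interaction already compares change between arms, and adjustment adds precision only.
- A reader might infer that gender is left out of the model. The third factor of the three-way ANOVA is not named. It could be gender, or the single- and dual-task conditions described under Balance assessment and gait analysis.
- A reader might infer that anyone with a missed visit is dropped. That is common behaviour for this kind of ANOVA, but the article states no such rule, and missing-data handling is commonly left to the full plan.
- The precision gain is small where pre-post correlation is very high. The article's reliabilities range from 0.40 (anterior-posterior platform oscillation) to 0.99 (Timed Up and Go, handgrip, stair climb). Used as ρ, these give ratios of 0.70 and 0.995. They are also test-retest figures, not correlations across a training period.
- The 0.3 SD retest gain is assumed, and familiarisation trials are planned for several tests, which may reduce it.

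That a separate analysis plan may exist does not remove the core point, because the article does state the trigger.

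**Conclusion.** The point holds in limited form. The article states a post-hoc trigger and never identifies the quantity that measures the training effect. On the natural reading, the group effect carries 1/3 to 2/3 of the post-test effect, and the time effect is significant in about 55% to 93% of trials from a 0.3 SD retest gain alone. The 1/3 to 2/3 share follows from the design for zero to full retention. The percentages rest on 16 completers per arm and on assumed effects and correlations.

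The stronger conclusion, that the planned analysis cannot detect the training effect or will ignore the interaction, is not supported: the ANOVA contains the interaction, and the wording allows a reading that uses it. Treating the pre-test as an outcome level is a loss of precision, with a variance ratio of about 0.75 at ρ = 0.5, 0.90 at 0.8 and near 1 for very high correlations. It is not a bias. The wording should be settled before analysis, because as it stands it allows a trial without a training effect to report significant improvement.

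**What to change.** Replace the post-hoc sentence with a named efficacy test:

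- Base efficacy on the baseline-adjusted INT1-CON, INT2-CON and INT1-INT2 contrasts at post-test. Use ANCOVA, or a mixed model on the post-test and follow-up values with group by visit and baseline value by visit.
- Apply the Bonferroni correction to those three contrasts for each outcome, so each is tested at 0.05 / 3 = 0.0167.
- Include gender as a factor, since the allocation uses it, or confirm that it is the third factor of the three-way ANOVA. In either case, name that third factor.
- Estimate detraining as the between-arm contrast of the change from post-test to follow-up.
- State that no efficacy conclusion will be drawn from the group or time main effect.

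If the ANOVA is kept, the minimum is to name the group-by-time interaction as the efficacy test and to tie the Bonferroni comparisons to it. The cost is analysis wording only. All the values needed are already to be collected, and neither the sample size nor the visit schedule changes.
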